### Frequency and duration of follow up

The current study will follow-up all women who participated in the trial at 5 years following surgery.

### Primary and secondary outcome measures

#### Primary outcome

Incidence of vaginal erosion or other serious adverse outcome of surgery (requiring additional treatment) over the 5 years following surgery.

#### Secondary outcomes

Objective outcome of SUI surgery at 5 years after index surgery.

Subjective outcome at 5 years following index SUI surgery.

Point prevalence of palpable tape, vaginal erosion or other serious adverse outcomes at 5 years after index SUI surgery.

### Outcome measures be measured at 5 year follow up

All outcomes will be measured at 5 years following index surgery.

#### Primary outcome: incidence of vaginal erosion or other serious adverse outcome

• **Incidence of vaginal erosion **will be determined by chart review and by standardised digital vaginal exam by a blinded examiner at the time of follow-up. The blinded examiner, a urogynaecology fellow, will be trained to undertake the standardized vaginal exam by MR. Any women who had additional treatment for vaginal erosion (any surgical treatment, or conservative treatment with vaginal estrogen), or who is found to have an erosion on digital exam, will be considered to have had a vaginal erosion.

• **Other serious adverse outcomes **will be defined as those occurring during the 5 years following index surgery which are considered to have a suspected "reasonable causal relationship" [59] with the TOT or TVT procedure. The adverse outcome will have resulted in further inpatient or outpatient treatment, an additional surgical or medical intervention, and/or cause persistent disability or incapacity. Possible adverse outcomes will include persistent groin pain and re-operation for SUI.

Women will be asked to recall any problems they believe they experienced as a result of surgery, and hospital charts will be reviewed for any possible adverse outcomes or complications. Details of additional treatment will be sought from the treating physician if treatment was provided elsewhere.

• **An independent adjudication committee **will be established to adjudicate all instances of a primary outcome (vaginal erosion or other serious adverse outcome). The adjudication committee will consist of three urogynaecologists not involved in the trial, from other institutions than the University of Calgary. They will be provided with all clinical details of the adverse outcome, with the cases blinded to group of allocation. The committee will be asked to judge whether each outcome can be defined as a serious adverse outcome and whether it has a "reasonable causal relationship" with the index surgery. Only if the adjudication committee agrees on both counts, will the adverse outcome be considered a primary outcome.

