### Methods for protecting against sources of bias

The initial trial was undertaken as a pragmatic trial [58]. Neither surgical team nor patient knew the next treatment allocation. Outcome measurement was not carried out blindly, but was conducted by a research nurse who was independent of clinical care. The vaginal examinations to palpate for tape erosion and pain were carried out by a clinician (MR) who had recruited 24 of the study patients. Although not informed of the patient's group of allocation at the time of vaginal examination, it became apparent that palpable tapes tended to be associated with TOT, and it was therefore not possible to maintain examiner blinding.

In the 5 year follow-up, similar considerations will apply. The research nurse who carried out the 12 month contacts and follow-up visits, and is therefore already known to study patients, will contact and follow all women at 5 years. The research nurse remains independent of clinical care. For the 5 year follow-up, all clinical examinations will be carried out by a urogynaecology clinical fellow who will be blinded to both group of allocation, and the presence of palpable tape at 12 months.

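### The interview for other serious adverse outcomes asks only about problems the woman herself blames on surgery, so some events outside the reviewed hospital charts may never reach the blinded committee

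*Protocol article*

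**What the plan says.** The section on the primary outcome (under the outcome measures at 5-year follow-up) describes several ways of finding events.

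- **Vaginal erosion** "will be determined by chart review and by standardised digital vaginal exam by a blinded examiner at the time of follow-up". Neither route depends on what the woman believes.
- **Other serious adverse outcomes** come from two parallel sources. For the interview, "Women will be asked to recall any problems they believe they experienced as a result of surgery". For the records, "hospital charts will be reviewed for any possible adverse outcomes or complications". Persistent groin pain and repeat incontinence surgery are the two named examples. The definition also takes in events needing outpatient or medical treatment and events causing lasting disability.
- **Care received elsewhere:** "Details of additional treatment will be sought from the treating physician if treatment was provided elsewhere".

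An independent committee of three urogynaecologists then rules on seriousness and causality. On what it sees: "They will be provided with all clinical details of the adverse outcome, with the cases blinded to group of allocation". On its power: "Only if the adjudication committee agrees on both counts, will the adverse outcome be considered a primary outcome".

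The section on protecting against bias says of the initial trial: "Outcome measurement was not carried out blindly, but was conducted by a research nurse who was independent of clinical care". It adds that similar considerations hold at 5 years, although the 5-year clinical examiner is blinded to arm and to the 12-month palpation finding. It states that patients did not know the next allocation. It does not say whether women know which procedure they had.

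**The concern.** The causal question is meant to be settled by blinded experts. The interview wording puts a lay version of the same question first. A woman treated by a family physician for groin or pelvic pain, who does not connect it with a tape placed up to five years earlier, can truthfully answer that she has had no problem from surgery. If her hospital chart is silent, nothing in the primary outcome section prompts a query to that physician, and the committee never sees the case. The committee can remove events but cannot restore one that was never submitted.

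Two things are at stake. Loss that is equal in both arms lowers the event rates and therefore the power, which the protocol already puts at only 70%. Loss that differs between arms would bias the primary safety comparison, and blinded adjudication could not correct it.

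**Working it through.** **1. Which events depend on the interview**

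| Event | Route that does not depend on the woman's belief |
|---|---|
| Erosion present at 5 years | Blinded digital examination |
| Erosion treated earlier | Chart review |
| Repeat incontinence surgery in the reviewed charts | Chart review for any possible event |
| Groin pain treated outside hospital | None stated in the primary outcome section |
| Persistent disability, never treated | None stated in the primary outcome section |

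Only the last two rows are exposed. The query to the treating physician asks for details of care elsewhere, and the only stated ways of learning of such care are the interview and the charts.

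**2. The protocol's own power figure**

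Inputs from the sample size section: 75 TOT and 84 TVT women, 27% versus 12%, two-sided chi-square test. The printed significance level of 0.05% is read as 5%, because read literally it gives only 14% power.

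Power = Φ[(|p₁ − p₂| − 1.96·s₀)/s₁], where

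- p̄ = (75 × 0.27 + 84 × 0.12)/159 = 0.1908
- s₀ = √[p̄(1 − p̄)(1/75 + 1/84)] = 0.0624
- s₁ = √[0.27 × 0.73/75 + 0.12 × 0.88/84] = 0.0623

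Power = Φ[(0.15 − 0.1223)/0.0623] = Φ(0.444) = 67.1%. Exact binomial enumeration of the uncorrected chi-square test gives 68.3%. Both are close to the stated 70%. The stated p-value also reproduces: z = 0.15/0.0624 = 2.40, p = 0.016.

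**3. Equal loss in both arms (assumed figures)**

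Let s be the share of events found only by interview, and suppose 20% of those are lost. Overall capture is then 1 − 0.2s in each arm.

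| s | Capture | Observed rates | Power |
|---|---|---|---|
| 0 | 100% | 27.0% v 12.0% | 67.1% |
| 1/4 | 95% | 25.65% v 11.4% | 64.4% |
| 1/3 | 93.3% | 25.2% v 11.2% | 63.4% |
| 1/2 | 90% | 24.3% v 10.8% | 61.5% |

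**4. Unequal loss when the arms do not differ (assumed figures)**

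Take a true rate of 20% in both arms, with 90% (TOT) and 70% (TVT) of interview-only events captured. Overall capture is 1 − 0.1s and 1 − 0.3s.

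| s | Observed rates | Two-sided rejection |
|---|---|---|
| 1/4 | 19.5% v 18.5% | 5.3% |
| 1/3 | 19.3% v 18.0% | 5.6% |
| 1/2 | 19.0% v 17.0% | 6.3% |

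These use the same normal approximation, adding both tails. Exact enumeration gives 5.3%, 5.6% and 6.4%. The documents supply neither s nor any capture fraction.

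**The case against.** The strongest reply is that the interview is one source among several. The same sentence adds a chart review for any possible event, erosion has a blinded examination, and repeat operations should appear in the charts. A reader might infer that the woman decides what the committee sees, or that primary outcome events are lost in general. The documents do not support that. The loss needs both conditions: no attribution by the woman and no entry in the reviewed charts. This part of the reply stands and sets the scope of the point.

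Second, a condensed article is not the data collection form. Where the authors print item wording, as for subjective cure, they show the tick boxes, and the real form may prompt by symptom. That is possible, but the article does state the basis of the interview, and that basis is the woman's belief about cause.

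Third, the health service utilization section has a somewhat broader patient question, acknowledges recall bias, and adds provincial hospital and physician payment data. That is fair, but none of it is said to feed adjudication.

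Fourth, a reader might infer a bias against TOT, since palpable tape (80% v 27%) and groin pain on palpation (15% v 6%) were more common there at 12 months. Those are examination findings. The documents do not say that women were told of them, or that women know their procedure. Unequal reporting is a possibility, and its direction is conjecture.

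**Conclusion.** The point holds in a limited form. For other serious adverse outcomes, the stated interview applies the woman's own causal judgement ahead of the committee's, and the primary outcome section gives no other trigger for events that lie outside the reviewed charts. No masking of women to procedure is described, so the loss could differ by arm, but neither its direction nor its size can be derived from the documents.

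Under the assumed fractions the effect is modest: about 3 to 6 percentage points of power, or a false rejection rate of up to about 6.3%. Applying the same fractions to every event in the composite would give 21.6% v 9.6% with 56% power, or 18% v 14% with about 11% false rejection. A reader might take those as the likely effect, but they ignore chart review and the blinded examination and are close to a worst case. The point deserves action because the remedy is cheap and the stated power leaves little to spare, not because a large bias has been shown.

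**What to change.** Replace the attribution-based question with a fixed set of neutral questions, put identically to all women whatever they think the cause. They should cover pelvic, groin, vaginal, urinary and sexual problems, and any related treatment or operation since the index surgery, including care outside hospital. A positive answer about treatment elsewhere then triggers the query to the treating physician.

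Send the committee every report that meets the protocol's existing seriousness criteria, together with relevant hits from the administrative data already planned for the health service utilization analysis. State that the committee alone judges causality.

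The cost is a reworded form and somewhat more cases to adjudicate, some of which will be unrelated to surgery. No extra visit or staff is needed.

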#### Health service utilization

Data will be sought from a variety of sources to ensure that we capture all condition-specific health services utilization related to repeat surgical intervention, as well as surgery and other treatment related to adverse events.

***Patients ***will be asked if they have needed any treatment for SUI or possible adverse effects of surgery in the 5 years following surgery. This approach may be limited because of recall bias, and therefore it will be only one of a number of approaches.

***Alberta Health Services***, the province-wide provider of health services, provided health care utilization data for our previous study, identifying inpatient and ambulatory hospital services. For the 5-year follow-up, we shall seek information in a similar way, using codes for diagnoses and procedures. For diagnoses we shall use ICD-10-CA, an enhanced version of ICD-10 developed by Canadian Institute for Health Information (CIHI) for morbidity classification in Canada [75]. For procedures we shall use the Canadian Classification of Health Interventions (CCI), the Canadian standard for classifying health care procedures [75]. Together these coding classifications will enable us to limit our evaluation to health service use that is related to possible consequence of SUI surgery.

***Alberta Heath and Wellness (AHW)***, the provincial health department, will be asked to provide data relating to the utilization of physician services. The Physician Payments Data File contains diagnostic data (ICD9-CM) which will allow us to identify condition-specific physician services utilization.

***Health services utilization ***will be described for each group. Comparisons between groups will include number of: visits to treat vaginal erosions; visits for treatments related to adverse events; and repeat surgeries for incontinence. Analyses comparing health services utilization between groups will use non-parametric methods.

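### The sources listed for the 5-year primary outcome do not include the provincial hospital and physician-payment records that the plan requests for the same kinds of event

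*Protocol article*

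**What the plan says.** The Primary outcome section defines the endpoint as "Incidence of vaginal erosion or other serious adverse outcome of surgery (requiring additional treatment) over the 5 years following surgery". The detailed outcome section then lists how events are found:

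- Erosion "will be determined by chart review and by standardised digital vaginal exam by a blinded examiner at the time of follow-up". Any surgical treatment of an erosion, or conservative treatment with vaginal estrogen, also makes the woman a case.
- Other serious adverse outcomes: "Women will be asked to recall any problems they believe they experienced as a result of surgery, and hospital charts will be reviewed". Inpatient or outpatient treatment and medical intervention all qualify.
- Care given elsewhere: "Details of additional treatment will be sought from the treating physician if treatment was provided elsewhere".
- Three outside urogynaecologists, blinded to allocation, adjudicate each case on seriousness and causal relationship.

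The Health service utilization section, under the economic evaluation, sets out to "capture all condition-specific health services utilization related to repeat surgical intervention, as well as surgery and other treatment related to adverse events". It starts with asking the women, and comments: "This approach may be limited because of recall bias, and therefore it will be only one of a number of approaches". It then adds provincial inpatient and ambulatory hospital data selected by diagnosis and procedure codes, and the provincial health department "will be asked to provide data relating to the utilization of physician services". From these data it will compare, by group, visits to treat erosions, visits for adverse-event treatment and repeat incontinence operations.

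**The concern.** The article describes event finding twice for overlapping events, and the primary safety question gets the narrower set of sources. The 5-year exam sees only what is present on the day. An erosion treated and healed in year 2 has to come from charts or from memory. Outpatient and conservative treatment qualifies as an event but need not appear in a hospital chart. The treating-physician inquiry can start only once the episode is known from recall or a chart. Adjudication can remove a candidate case but cannot add one that nobody submitted.

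If events are missed equally in both arms, the study loses power that it can ill afford to lose. If they are missed unequally, the comparison itself is biased. Unequal reporting is possible because recall is not blinded in any way the article describes. On the initial trial, the section on protecting against bias says: "Outcome measurement was not carried out blindly, but was conducted by a research nurse who was independent of clinical care", and it states that similar considerations apply at 5 years, with the same nurse following the women. Coded records do not depend on a woman's memory or on who asks her.

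**Working it through.** **Sources set side by side**

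| Source | Primary outcome | Utilization analysis |
|---|---|---|
| Blinded exam at 5 years | yes (erosion) | no |
| Hospital chart review | yes | not listed |
| Women's report | yes | yes, with a caution about recall bias |
| Treating-physician inquiry | yes, if care was elsewhere | not listed |
| Provincial inpatient and ambulatory hospital data | not listed | yes, to be sought |
| Provincial physician-payment file | not listed | yes, to be asked for |

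No section links the last two rows to the primary outcome or to the adjudication committee.

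**Inputs (Sample size and justification):** 75 TOT and 84 TVT women after 20% loss (94 × 0.8 = 75.2; 105 × 0.8 = 84.0); event rates 27% and 12%; stated power 70%; stated p-value 0.016. The two-sided level is printed as 0.05%. Taken literally (0.0005) it would give about 14% power, so 0.05 is used here.

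**The plan's own figures first.** Pooled proportion = (75 × 0.27 + 84 × 0.12)/159 = 30.33/159 = 0.1908.

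- SE under the null = √[0.1908 × 0.8092 × (1/75 + 1/84)] = 0.0624.
- z = 0.15/0.0624 = 2.40, p = 0.0163. The stated 0.016 reproduces.
- SE under the alternative = √(0.27 × 0.73/75 + 0.12 × 0.88/84) = 0.0623.
- Power = Φ[(0.15 − 1.96 × 0.0624)/0.0623] = Φ(0.444) = 67.1%. Exact enumeration of the uncorrected chi-square test gives 68.3%, within 2 points of the stated 70%.

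**Equal incomplete capture.** The documents give no capture rate, so the share s of events found is an assumption. Both rates are multiplied by s and the same power formula is applied. Missed events = 30.33 × (1 − s).

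| s | TOT | TVT | Events missed of about 30 | Power |
|---|---|---|---|---|
| 1.00 | 27.0% | 12.0% | 0 | 67.1% |
| 0.90 | 24.3% | 10.8% | 3.0 | 61.5% |
| 0.80 | 21.6% | 9.6% | 6.1 | 55.6% |
| 0.75 | 20.25% | 9.0% | 7.6 | 52.5% (52.48) |

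The risk ratio stays at 0.27/0.12 = 2.25 throughout.

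**Unequal capture (assumed).**

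- 80% found in TOT, 100% in TVT: 0.216/0.12 = 1.80.
- 100% found in TOT, 80% in TVT: 0.27/0.096 = 2.81.

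**The case against.** The strongest reply is that the primary outcome does not rest on recall alone. Erosion has a blinded exam and chart review, other events have charts and a physician inquiry, and recall is therefore one of several approaches here too. That is correct, and the exam in particular finds erosions present at 5 years without any help from memory. It leaves open only the events that were treated and resolved, lie outside the reviewed charts and are not recalled.

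Non-use of the records is also inferred from a list that is not called exclusive, and a journal article may leave case-finding detail to the full protocol. This has force. However, the article does name its sources for the primary outcome and names further sources for the same kinds of event a few sections later, so the missing link can fairly be raised. The records are to be requested and are not yet in hand.

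A reader might infer more than the documents support:

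- *That the safety comparison is biased against TOT*, for example because women who knew of a palpable tape report more. Nothing says that women were told of a palpable tape. The 5-year examiner is blinded to allocation and to the 12-month finding, and adjudication is blinded. Bias in either direction is possible.
- *That the two parts of the study contradict each other if their counts differ.* One counts visits and operations, the other counts women with adjudicated, causally related events. Some difference is expected by design.
- *That the records would close the gap.* They are described as service and diagnosis data, not drug dispensing, and a code alone does not give the committee the clinical detail it needs to judge causality.

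**Conclusion.** The concern holds as a cheap improvement to event finding, not as an error that invalidates the primary outcome. A cumulative, largely treatment-defined endpoint should draw on the records already being requested for the same treatments, particularly as the plan itself cautions against reliance on recall. The listed sources do not include them.

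The size is unknown. The power losses (67% to 62%, 56% or 52%) and the shifted risk ratios (1.80 or 2.81 against 2.25) rest on assumed capture shares. They apply the shortfall to all events, including exam-detected erosions and re-operations found in charts, for which capture may well be better. They show how little slack there is at a planned power of 70%; they do not estimate what will be lost.

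**What to change.** In the section defining the primary outcome, name the provincial hospital and physician-payment records as a supplementary source of candidate primary events:

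1. Apply the code lists used for the utilization analysis identically to both arms.
2. Confirm each hit against clinical records, then send it to the adjudication committee with allocation removed.
3. Keep the existing sources; the records add to them and do not replace them.
4. Keep the primary comparison to women who have the 5-year exam. Women who allow record access but do not attend may enter a sensitivity analysis. Putting them in the primary comparison would make ascertainment depend on attendance, because an untreated erosion cannot be found without the exam. Non-response to the request for 5-year contact already differs by arm: 16/94 (17%) TOT and 12/105 (11%) TVT.

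The cost is wording in the outcome definition, consent and data request, retrieval of clinical records for each hit, and some extra adjudication. Conservative treatment such as vaginal estrogen may still be missed where the visit is not coded specifically, and the report should say so.

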#### Secondary outcomes

##### Objective outcome of SUI surgery at 5 years after index surgery, measured by pad test

Objective evidence of SUI at 5 years following surgery will be obtained using a standardised pad test (as used in our 12 month follow-up [16]), as follows.

• Retrograde filling of bladder with 300 ml sterile water

• Pre-weighed collecting device (pad) is put on and the test period begins

• During a 15 minute period the subject performs the following activities: walk up and down 1 flight of stairs; standing up from sitting, 10 times; coughing vigorously, 10 times; running on the spot for 1 min; bending to pick up small object from floor, 5 times; washing hands in running water for 1 min

• At the end of the test the collecting device is removed and weighed

• If test is representative, subject undertakes uroflow evaluation (check for voiding dysfunction)

Women will be considered "cured" if the pad weight gain is less than 1 g over the test period. This definition of cure was used in our earlier follow-up [16], allowing comparison with that study. This definition has also been used in other incontinence RCTs [34,60].

